**Methods/Design:**

A web-based patient registration system 'Registrationsystem Oncological GYnecology' (ROGY) is used by gynecologists in the South of the Netherlands since 2006. A personalized SCP can automatically be generated out of ROGY. In this pragmatic cluster randomized controlled trial, 12 hospitals are randomized to either 'usual care' or 'SCP care'. In patients with 'usual care', the gynecologist provides care as usual. In patients with 'SCP care', information about the tumor stage and treatment is personally discussed with the patient and a document is handed to the patient. Prospectively, all patients diagnosed with endometrial or ovarian cancer in the participating hospitals will be approached for study participation. Patients will complete questionnaires after surgery, and before additional treatment, and after 6, 12, 18 and 24 months. In addition, health care providers will be asked their opinion about implementation of SCP care. Primary outcome is defined as patient satisfaction with information provision and care. Secondary outcomes are illness perception, health-related quality of life, health care use, prevalence, course and referral rate of survivors with psychosocial distress, and health care providers' evaluation of SCP care.

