## Methods/Design

### Objectives and hypotheses

The aim of the proposed study is to assess the impact of SCP care on patient and health care provider reported outcomes in routine clinical practice. Primary outcomes include patients' satisfaction with information provision, and satisfaction with care. Secondary outcomes include patients' health-related quality of life, illness perception, health care use, prevalence, course and referral rate of patients with psychosocial distress, and health care providers' evaluation of the (implementation of the) SCP.

It is hypothesized that patients who receive SCP care report better satisfaction with information provision, better satisfaction with care, and more adequate illness perception than those who receive usual care. It is furthermore hypothesized that patients who receive SCP care will report a higher health care use compared to those receiving usual care [14]. In addition, it is expected that patients who receive the SCP will report less anxiety, less depression or psychosocial stress and better HRQoL. However, there may be subgroups (dependent on patient characteristics, such as age, education, and personality) that will be influenced in a negative way when receiving more information than they can handle. Finally, it is hypothesized that patients who receive SCP care are more adequately referred to other health care services when they have high distress levels compared to those who receive usual care.

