### Patient reported outcomes

Outcomes will be assessed with standardized and validated measures shown to have acceptable psychometric properties.

*Satisfaction with information provision *will be measured using the EORTC-INFO26 [21] module. This questionnaire aims to evaluate the (satisfaction with) information received by cancer patients on different areas of the disease, diagnosis, treatment and care, and some qualitative aspects, for instance wishes for more information. The questionnaire contains the following scales: (a) Information about the disease; (b) Information about medical tests; (c) Information about treatment; (d) Information on other services, and single items: (a) Written information; (b) Information on CDs or tape/video; (c) Satisfaction with the amount of information; (d) Desire for more information; (e) Desire for less information; (f) Helpfulness of information. Furthermore, a more specific question will be added about whether patients have received an SCP, to control for physician compliance with the provision of SCP care.

*Cancer specific HRQoL *will be measured with the EORTC QLQ-C30 [22]. Much of the content of the questionnaire is appropriate for extended monitoring of health status, including scales assessing physical, cognitive and emotional functioning, fatigue and sleep problems, and overall health and quality of life. This core instrument is supplemented by a condition-specific questionnaire module. For endometrial cancer, the EORTC-EN24 [23] module will be used. This module assesses lymphoedema, urological symptoms, gastrointestinal symptoms, body image, sexual/vaginal symptoms, back/pelvic pain, and chemotherapy side effects. For ovarian cancer, the EORTC-OV28 module [24] will be used, which measures abdominal/gastrointestinal symptoms, peripheral neuropathy, other chemotherapy side-effects, hormonal/menopausal symptoms, body image, attitude to disease/treatment and sexual functioning.

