*Satisfaction with care *will be measured with the EORTC IN-PATSAT32 [25]. This questionnaire was designed to assess cancer patients' perception of the quality of medical care, nursing care and care organization and services received in the hospital. The EORTC IN-PATSAT32 contains 11 multi-item and 3 single-item scales. These include the doctors' technical skills, interpersonal skills, information provision, and availability; the nurses' technical skills, interpersonal skills, information provision, and availability; the other hospital staff's interpersonal skills and information provision scale; the exchange of information single-item scale; the waiting time; the hospital access; the comfort single-item scale; and the general satisfaction single-item scale.

*Illness perception *will be measured using the Brief Illness Perception Questionnaire (B-IPQ) [26]. The scale has 9 items, measuring (a) cognitive representations (consequences, timeline, personal control, treatment control, identity); (b) emotional representations (concern, emotion); (c) illness comprehensibility; and (d) an open-ended response item on the 3 most important causal factors of illness.

*Comorbidity at the time of questionnaire completion *will be assessed by the adapted Self-administered Comorbidity Questionnaire (SCQ) [27]. Patients will be asked to identify comorbid conditions developed in the past 12 months. The adapted SCQ lists 14 medical conditions (with the option to list up to 3 additional conditions), and assesses if the patient is treated for the comorbid condition and the perceived impact on the patients' functioning.

*Anxiety and depression *will be assessed using the Hospital Anxiety and Depression Scale (HADS) [28]. The HADS has 14-items, with 7 items each for anxiety and depression. Each item is scored from 0 to 3, where a score of 3 represents a state corresponding to the worst anxiety or depression. The sum of these items produces two subscales ranging from 0 to 21. A score of 8 will be used as a cut-off value for both depression and anxiety [28].

*Physical and mental fatigue *will be measured using the Fatigue Assessment Scale (FAS) [29], which consists of 10-items with 5 items each reflecting physical and mental fatigue. The items are scored on a 5-point response scale ranging from 1 (never) to 5 (always).

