*Personality *will be measured with the DS14 [30] which has 14 items ranged on a 5-point response scale ranging from 0 (false) to 4 (true). Seven of these items refer to 'Negative Affectivity' or the tendency to experience negative emotions in general (e.g., 'I am often down in the dumps or I often find myself worrying about something'). The remaining 7 items refer to the patient's level of 'Social Inhibition', or the tendency to inhibit the expression of emotion/behavior in social relationships (e.g., 'I am a closed kind of person or I often feel inhibited in social interactions'). According to previously published cut-off scores, patients were diagnosed as Type D if they scored ≥10 on both the Negative Affectivity and Social Inhibition scales.

*Health care utilization *will be assessed by patients' frequency and reason (cancer-related or not) for contact with their general practitioner or medical specialist in the past 12 months. Patients will be asked whether they have been referred to other health care services.

Additional measures include demographic and socioeconomic variables such as age, education, marital status, and employment status, and clinical variables such as cancer stage at diagnosis, time after diagnosis, and initial treatment. All measures will be collected at the beginning of the trial, and at 6, 12, 18 and 24 months after diagnosis.

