### Statistical analysis

Analyses will be performed adhering to the intention-to-treat principle. Descriptive statistics will be used to summarize characteristics of both hospitals and patients. Characteristics of patients (i.e., age, type of cancer, stage, treatment, socio-economic status, marital status, educational level, employment status) and hospitals (i.e., number of endometrial and ovarian cancer patients, whether a hospital is a training hospital) will be compared at baseline between the intervention and usual care group, by regression analyses.

Linear regression models will be used to analyze continuous outcome variables, and logistic models for binary outcome variables. All analyses will be adjusted for hospital, baseline values of the outcome measure, and baseline variables which differ to a clinically significant extent between groups. Differential effects of SCP care by age, type of cancer and baseline levels of the outcomes of interest will be assessed for the outcome measures by adding terms for the interaction between age, educational level, personality, type of cancer and baseline levels and care arm to the regression models.

A multilevel modeling approach [36] will be applied to evaluate differences between the intervention group and the control group. This approach will be used to take into account the clustering at the hospital level [37]. All statistical tests will be two-sided and considered significant if *p*<0.05. Repeated measures analysis using generalized estimating equations will be conducted to account for the intra-patient dependency of the repeated measures [38]. Differences in effect of the SCP care and usual care at the different time points will also be investigated [38].

Missing outcome data will be assumed to be 'missing at random' (MAR), conditional on key predictors of 'missingness' (in particular baseline values of the outcome variables of interest, and care arm). Clinically meaningful differences will be determined with Norman's 'rule of thumb', whereby a difference of ≈0.5 *SD *indicates a threshold of discriminant change in health status scores of a chronic illness [35].

Routinely collected data from the population-based Eindhoven Cancer Registry (ECR) and ROGY on patient and tumor characteristics will allow for the comparison of respondents, non-respondents and patients with unverifiable addresses, using t-tests for continuous variables and Chi-square analyses for categorical variables.

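### Two questionnaire-level primary outcomes, 24 scores, no named primary score or contrast, and unadjusted p<0.05 throughout leave the error rate of the primary claim undefined

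*Protocol article*

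**What the plan says.** **Primary outcomes.** Objectives and hypotheses: "Primary outcomes include patients' satisfaction with information provision, and satisfaction with care". Neither is ranked above the other. The abstract uses the singular: "Primary outcome is defined as patient satisfaction with information provision and care".

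**Instruments.** Under Patient reported outcomes, satisfaction with information is measured with the EORTC-INFO26. Its scales are introduced by "The questionnaire contains the following scales: (a) Information about the disease; (b) Information about medical tests" and continue to (d). Six single items follow, the last three being "d) Desire for more information; (e) Desire for less information; (f) Helpfulness of information". Satisfaction with care is measured with another instrument: "The EORTC IN-PATSAT32 contains 11 multi-item and 3 single-item scales". No total score or lead scale is named for either.

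**Timing.** "All measures will be collected at the beginning of the trial, and at 6, 12, 18 and 24 months after diagnosis". None of the follow-up times is called primary.

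**Analysis.** Statistical analysis plans multilevel and repeated-measures models and adds: "Differences in effect of the SCP care and usual care at the different time points will also be investigated". The decision rule is "All statistical tests will be two-sided and considered significant if" p<0.05. The section contains no ordering of tests, no adjustment, and no requirement that both outcomes succeed.

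**The concern.** A confirmatory claim needs a defined test. Here the primary outcome stays at the level of whole questionnaires, while the significance rule applies to each individual test. A reader of the results could not tell from the article which score, over which period, decides whether the primary hypothesis was met. Several answers are compatible with the text, and they carry very different error rates.

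The consequence is practical. The Discussion says that evidence of feasibility and effectiveness could be used to persuade providers and insurers to adopt SCP care. If one favourable score out of many were presented as the primary result, that case could rest on chance. The sample size section does not settle the matter: its 0.5 SD effect is a generic standardised difference for one test, tied to no particular score or time.

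**Working it through.** **1. The article's own power figure.** About 300 analysed patients (337 × 0.9 = 303), taken as 150 per arm, effect 0.5 SD, two-sided 0.05, one test.
- Ignoring clustering: 0.5 × √(150/2) = 4.330; power = Φ(4.330 − 1.960) = 0.991, against the stated 0.98.
- No ICC is stated. Assuming 300/12 = 25 patients per hospital and ICC 0.007, the design effect is 1 + 24 × 0.007 = 1.168 and power is 0.980.
- For the 150-patient figure (12.5 per hospital), the same ICC gives 0.838, against the stated 0.83.

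Both figures are therefore consistent with a single test at 0.05 and a small ICC.

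**2. Number of primary scores.**
- INFO26: 4 scales + 6 single items = 10.
- IN-PATSAT32: 11 + 3 = 14. The listed scales also count to 14: doctors 4, nurses 4, other staff 1, and one each for exchange of information, waiting time, access, comfort and general satisfaction.
- Total: 10 + 14 = 24.

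**3. Chance of at least one false positive if every score were tested once.** For k independent tests this is 1 − 0.95^k in either direction and 1 − 0.975^k in the direction of benefit only. The correlated rows assume a common correlation r between the 24 test statistics. The documents give no correlations, so r is varied.

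| Tests | Assumed r | Either direction | Benefit only |
|---|---|---|---|
| 2 (one per construct) | 0 | 9.8% | 4.9% |
| 24 (one time point) | 0 | 71% | 46% |
| 24 | 0.3 | 59% | 31% |
| 24 | 0.5 | 46% | 23% |
| 24 | 0.7 | 31% | 16% |

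The benefit-only column counts every score as having a benefit direction. The article states none for the items on wanting more or less information, so that column is slightly high.

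**4. Why the contrast must be fixed too.** Take one score per construct, but let each of the four follow-ups count. With assumed correlations of 0.2 to 0.6 between scores and 0.5 to 0.8 across time, the rate is 29% down to 19% in either direction and 15% down to 10% for benefit only. The higher rates go with the weaker correlations.

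**5. Power cost of a two-test procedure.** In the worst case Holm's first step uses 0.025. Calculated with a noncentral t on 10 degrees of freedom (12 hospitals − 2), 25 patients per hospital and effect 0.5 SD:

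| Assumed ICC | Design effect | Patients per arm ÷ design effect | Power at 0.05 | Power at 0.025 |
|---|---|---|---|---|
| 0.008 | 1.192 | 125.8 | 0.95 | 0.89 |
| 0.02 | 1.480 | 101.4 | 0.89 | 0.80 |

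For comparison, Bonferroni over all 24 scores (0.05/24) would leave 0.82 at ICC 0.007 and 0.59 at ICC 0.03, even on the more favourable normal approximation.

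**The case against.** The strongest reply is that the article never says one sub-scale at one visit is enough. The hypotheses are stated by construct, and the 0.05 rule says only when a single test is significant. A reader might infer that any of 24 × 4 = 96 comparisons could win the trial. The text does not support that: no such rule appears, and the time-point comparisons are introduced as something examined in addition to the repeated-measures analysis. This part of the reply stands, so the 24-score rates above are conditional and no 96-test rate is claimed.

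A reader might also take 71% as the chance of falsely claiming that SCP care helps. That figure counts false harm as well; the benefit-only figure is 46%. At the level of two constructs with one test each, benefit-only error is just under 5%. That also stands.

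Three further points limit the concern:
- The abstract and the methods name the same two constructs. The singular against the plural is wording, not a contradiction.
- The article adds a threshold of about 0.5 SD for a clinically meaningful difference. This would restrain the interpretation of an isolated small p-value, but it is not an error-rate control.
- It may seem that items such as hospital access or waiting time cannot respond to an SCP. That is a judgement the article does not settle, and the point does not need it.

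Finally, a condensed article may leave the choice of score and the multiplicity procedure to a fuller document. This has force for detail. It does not remove the point, because the article itself fixes 0.05 for all tests and defines the primary outcome at questionnaire level. Nothing elsewhere in it narrows either.

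**Conclusion.** The point holds in limited form. The article names two unranked primary constructs, 24 scores and four follow-ups, selects no primary score or contrast, and applies an unadjusted two-sided 0.05 to every test. The error rate of the primary claim is therefore not fixed. It ranges from about 9.8% in either direction (4.9% for benefit only), with one independent test per construct, to 71% (46%) if any of 24 independent scores at one time could count. Under assumed equicorrelations of 0.3 to 0.7 the 24-score figures fall to between 59% and 31% (31% and 16%).

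The absence of a defined primary test and of any adjustment is certain from the text. The size of the inflation is not: it depends on a success rule the article does not give and on assumed correlations. The power statement is not wrong for a single test; it simply does not cover an adjusted primary analysis. This is a cheap improvement to the wording, not evidence that the design fails.

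**What to change.** In Objectives and hypotheses and in Statistical analysis:

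1. Name one score per construct from those already collected. Whether this is a single item, a multi-item scale or an agreed composite is the sponsor's choice.
2. Name one contrast for both: the arm effect averaged over 6 to 24 months, or the effect at one fixed follow-up.
3. Test the two with Holm's procedure at an overall two-sided 0.05, and say what is claimed if only one succeeds.
4. Label the remaining scores and the time-specific contrasts secondary, without a confirmatory claim.

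No new data or patients are needed. The cost is power at the first Holm step: about 0.95 to 0.89 at an assumed ICC of 0.008, or 0.89 to 0.80 at 0.02. Since inclusion began in April 2011, the change should be dated and made without sight of outcome data by arm.

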### Ethical considerations

The study protocol has been approved by the medical research ethics committees of the participating centers (Medical Research Ethics Committee reference number: NL33429.008.10). The study will be conducted according to the Declaration of Helsinki, as amended in 2008 by the World Medical Association, and all patients will be informed about the purpose, rights, and possible benefits/risks of the study. Study participation of patients is voluntary and can be cancelled at any time without provision of reasons and without any consequences. Patients can call a psychologist, an epidemiologist, or an independent general practitioner for more information about the study.

### Data security/disclosure of original documents

Confidentiality and anonymity of participants will be guaranteed with the assignation of a study number to each participant. As such, returned questionnaires have no names attached and will be linked to data from the ECR by study number. Therefore, it will not be possible for the researchers to track participants' names with the study numbers. The results of the patient questionnaires are not accessible to the gynecologists or other health care providers. Questionnaires are directly mailed to the study center by the patients. Returned questionnaires will be stored in a secured location for five years. Only direct members of the internal study team can access the respective files.

## Discussion

The number cancer survivors that are confronted with adverse long-term or late effects is rapidly increasing. These cancer survivors remain at risk for adverse long-term or late effects of cancer diagnosis and treatment, and often do not know how to interpret their physical or psychosocial problems, or where to go for support. Providing patients with an SCP may be an empowering and enabling instrument, by facilitating better understanding and self-care by the patient. However, evidence concerning the effects of the implementation of the SCP in daily clinical practice is lacking. It is therefore necessary to assess the impact of SCP care in routine clinical practice before its large-scale implementation.

If this study shows that SCP care is feasible and effective, this scientific evidence can be used to convince cancer survivors' health care providers and health insurance companies about the benefits of implementing SCP care. The results will help to gain insight into the impact of SCP care on patient reported outcomes, and on the evaluation of cancer survivors and health care providers of the different elements of the SCP. Therefore, results will contribute to efforts to improve quality of care for cancer survivors.

## Trial status

The inclusion of patients started April 2011. The initial patient inclusion will be completed in approximately one year. Patients will be followed for two years.

## List of abbreviations

CCCS: Comprehensive Cancer Center South; ECR: Eindhoven Cancer Registry; HRQoL: Health-Related Quality of Life; IOM: American Institute of Medicine; MAR: Missing At Random; NCCS: National Coalition for Cancer Survivorship; OOG-CCCS: Organization Oncologic Gynecology of the Comprehensive Cancer Center South; RCT: Randomized Controlled Trial; ROGY: Registrationsystem Oncological GYnecology; SCP: Survivorship Care Plan.

## Links

ClinicalTrials.gov http://www.ClinicalTrials.gov

National Coalition for Cancer Survivorship http://www.canceradvocacy.org

CONSORT recommendations for reporting on trials http://www.consort-statement.org

PROFILES http://www.profielstudie.nl

Oncoline - Cancer Clinical Practice Guidelines http://www.oncoline.nl
